### Sample size and justification

The primary outcome HbA1c after 1 year is used to test whether eHealth support is non-inferior to face-to-face support. The non-inferiority margin (delta) for HbA1c is set at 8 mmol/mol (0.8%). This margin is based on the clinically relevant HbA1c reduction leading to a lower risk of microvascular complications in patients with newly diagnosed type 2 diabetes.^28^ This margin is further justified by the fact that commonly used glucose-lowering medications, such as SGLT2 inhibitors and metformin, typically achieve a mean HbA1c reduction of at least 8 mmol/mol compared with placebo,^29^ which means that a declaration of non-inferiority implies that eHealth support would have a non-zero effect. In the DiRECT study, the mean HbA1c level after 1 year was 50.6 mmol/mol (6.8%) with a SD of 13.3 mmol/mol (1.2%).^18^ If we assume the same SD in the present study, we need to randomise 96 study participants to achieve sufficient power in a test procedure based on the estimation of a CI based on the t-distribution as calculated with the *Sealed Envelope* online calculator.^30^ In the DiRECT study, 22% of participants dropped out of the intervention, but only 8% had HbA1c levels unavailable after 1 year. We therefore expect a drop-out rate of 10% and plan to include 106 participants in our study. For the calculation, we used a significance level (alpha) of 0.05 and a target power (1-beta) of 90%.

The main objective of this randomised trial is to demonstrate the non-inferiority of eHealth support compared with face-to-face support. HbA1c is a relevant surrogate measure for diabetes remission, and we therefore believe that HbA1c as a continuous variable rather than diabetes remission as a dichotomous outcome represents an appropriate trade-off between the project requirements and the costs and benefits for participants to investigate the non-inferiority of eHealth support compared with face-to-face support.

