### Objective

Our primary hypothesis is that eHealth support is non-inferior to face-to-face support in helping patients with type 2 diabetes achieve remission through calorie restriction. Our secondary hypothesis is that eHealth support will be more cost-effective than face-to-face support.

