### Statistical analyses

For the primary outcome, the continuous variable HbA1c is analysed for non-inferiority using ANCOVA, with HbA1c at 12 months as the dependent variable and the group as the independent variable. The analysis will be adjusted for baseline HbA1c and study centre to account for stratified randomisation. The non-inferiority margin is 8 mmol/mol (0.8%). If a participant is taking medication to lower blood glucose, that participant’s HbA1c will be adjusted for the average blood glucose-lowering effect of the medication used, according to the meta-analysis by Tsapas and colleagues.^29^ The analysis is performed according to the intention-to-treat principle with imputation of missing values using multivariate imputation by chained equations.^31^ The same analysis will be performed on the full analysis set, that is, all randomised participants with HbA1c measurements at baseline and 12 months, as a sensitivity analysis. The intention-to-treat population is defined as all study participants that were randomised.

The secondary outcome diabetes remission in per cent will be tested for non-inferiority with a non-inferiority margin of 10 percentage points, followed by a test for superiority. The other secondary outcomes will be tested for superiority only.

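### The margin rationale does not support a non-zero eHealth effect, and the primary hypothesis is worded as remission while the test covers only mean HbA1c within 8 mmol/mol

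*Protocol article*

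**What the plan says.** All references are to the protocol article.

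- **Sample size and justification** sets the margin at 8 mmol/mol, with 0.8% in brackets, and gives two reasons. The first is clinical: "This margin is based on the clinically relevant HbA1c reduction leading to a lower risk of microvascular complications". The second is that SGLT2 inhibitors and metformin "typically achieve a mean HbA1c reduction of at least 8 mmol/mol compared with placebo", "which means that a declaration of non-inferiority implies that eHealth support would have a non-zero effect".
- The same section takes a 1-year mean of 50.6 mmol/mol (6.8%) and an SD of 13.3 mmol/mol (1.2%) from the reference trial (DiRECT). It uses alpha 0.05, without stating sidedness, and 90% power. This leads to 96 participants, raised to 106. It calls HbA1c a relevant surrogate for remission.
- **Objective** (and the Abstract in similar words) states: "Our primary hypothesis is that eHealth support is non-inferior to face-to-face support in helping patients with type 2 diabetes achieve remission through calorie restriction".
- **Primary outcome** is continuous HbA1c at 12 months.
- **Statistical analyses** gives remission its own secondary test: it is "tested for non-inferiority with a non-inferiority margin of 10 percentage points".
- **Strengths and limitations** discloses that 8 mmol/mol is wider than the 4 mmol/mol common in drug trials.

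**The concern.** Two statements govern what the trial may conclude, and neither matches the test.

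First, a non-inferiority result shows that the new arm retains some effect only when the margin is no larger than the comparator's own effect over no treatment. Here the comparator is face-to-face support, but the effect cited is that of two drugs over placebo.

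Second, the hypothesis speaks of achieving remission, while the decision rests on mean HbA1c with a margin of 8 mmol/mol. The protocol separately says how much remission loss it would tolerate. If the two margins are far apart, a pass on HbA1c could be reported under the hypothesis wording as non-inferior remission without the remission limit having been met.

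**Working it through.** **Step 1. Reproduce the sample size.** With SD 13.3, margin 8, no true difference, one-sided alpha 0.05 and 90% power:

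n per arm = 2 × 13.3² × (1.645 + 1.2816)² / 8² = 2 × 176.89 × 8.564 / 64 = 47.3, so 48 per arm and 96 in total. This matches. One-sided 0.025 gives 59 per arm (118), which does not. The stated 0.05 is therefore read as one-sided below.

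**Step 2. The non-zero inference.** Let F be the HbA1c reduction of face-to-face support over no programme, E that of eHealth, and D = F − E. Declaring non-inferiority supports D < 8, hence E > F − 8. This guarantees E > 0 only if F is at least 8. The article gives 1-year results for the reference trial's intervention arm (mean 50.6, remission 46%) but no HbA1c difference from control. The drug-versus-placebo reduction is not F, so the premise is missing.

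**Step 3. Remission at the HbA1c margin.** Assume normal HbA1c, a uniform shift, and remission as HbA1c < 48 only.

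- At mean 50.6: Φ((48 − 50.6)/13.3) = 42.3%.
- At mean 58.6: Φ((48 − 58.6)/13.3) = 21.3%.
- Loss: 21.0 points.
- With the mean set to 49.34 so that remission equals the reported 46%: 46% falls to 24.1%, a loss of 21.9 points.

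Sensitivity of the loss:

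| Variant | Loss (points) |
|---|---|
| SD 10 | 25.3 |
| SD 18 | 16.5 |
| Lognormal, same CV | 21.0 |
| Lognormal, shifted | 25.3 |
| Gamma with floor 25 or 30 mmol/mol | 26.7 or 28.6 |

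Every variant exceeds 10 points.

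**Step 4. The 10-point remission margin in HbA1c units.** The shift that costs 10 points is 3.53 mmol/mol (3.43 when calibrated to 46%). The HbA1c margin is thus 8 / 3.53 = 2.3 times as wide.

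**Step 5. How often each loss would pass.** At 48 per arm, SE = 13.3 × √(2/48) = 2.715.

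- True loss of 8 mmol/mol: passes with probability alpha, 5%.
- True loss of 3.53 mmol/mol: Φ((8 − 3.53)/2.715 − 1.645) = 50%. At 53 per arm (106/2) it is 53%. At one-sided 0.025 the figures are 38% and 41%.
- Largest observed difference that passes: 8 − 1.645 × 2.715 = 3.5 mmol/mol.

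**Step 6. Power of the remission test.** With 46% in both arms, SE at 48 per arm = √(2 × 0.46 × 0.54/48) = 0.1017. Power = Φ(0.10/0.1017 − 1.645) = 25%; at 53 per arm it is 27%. For 90% power it would need 426 per arm.

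**Step 7. Units.** By the article's own SD pair, 8 × 1.2/13.3 = 0.72%. By its level pairs (43 = 6.1%, 50.6 = 6.8%), 8 × 0.7/7.6 = 0.74%. Both round to 0.7%. Read literally, 0.8% would be 0.8 × 13.3/1.2 = 8.9 mmol/mol.

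**The case against.** The strongest reply has five parts.

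- **The 21 points are a boundary, not a forecast.** This stands. A reader might infer that a passing trial would have lost half of its remissions. The documents do not support that: such a loss passes about 5% of the time, and the largest passing observed difference, about 3.5 mmol/mol, corresponds to about 10 points. Non-inferiority for remission nevertheless depends on what the confidence limit excludes, and a pass on HbA1c does not exclude losses beyond 10 points.
- **The non-zero claim may be true.** This also stands. The section on unmet need says the face-to-face programme has been shown to be effective, and its effect over control may lie in the cited sources. The sentence lacks a premise; it is not refuted.
- **A margin equal to a clinically relevant difference is legitimate.** Agreed. One might infer that the first rationale makes a relevant loss acceptable, but a pass rules out a loss of that size. Whether smaller losses matter is a judgement, and the article discloses that its margin is wide.
- **Remission is handled separately.** In part. The primary outcome is clearly continuous HbA1c, the choice is explained, and nothing in the article says that passing on HbA1c licenses a remission claim. But the hypothesis wording invites that claim, and calling HbA1c a surrogate does not make the two margins equivalent.
- **The mapping is crude.** It ignores the no-medication condition and the medication adjustment of the primary outcome. That limits its precision. The direction held in every variant tried.

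**Conclusion.** The concern holds as a matter of what may be claimed. The inference to a non-zero effect is unsupported as written, because the comparator's HbA1c effect over no programme is absent. This finding needs no model.

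The primary hypothesis is worded for remission, but its test tolerates, at the limit, an HbA1c loss worth about 21 to 22 remission points (about 16 to 25 across SDs of 10 to 18 and lognormal shapes, up to 29 with strongly skewed gamma shapes). The protocol's own remission margin is 10 points. A true shift already at that remission limit would pass the primary test about half the time. These figures rest on a uniform shift, the reference trial's mean and SD, one-sided 0.05, an unadjusted comparison, and remission defined by HbA1c alone.

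The bracketed 0.8% is an editorial slip; 8 mmol/mol reproduces the sample size and is the decision limit. The point deserves correction before analysis, but it does not undermine the margin, the sample size or the analysis method.

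**What to change.** 1. In Sample size and justification, delete the inference to a non-zero effect. Alternatively, rebase it on the lower confidence limit of the face-to-face programme's HbA1c effect versus control in the reference trial, and show that this limit is at least 8 mmol/mol.
2. In the Abstract and Objective, and in the planned conclusion, state the primary claim as non-inferiority in HbA1c within 8 mmol/mol. Claim non-inferior remission only if the 10-point remission test is met.
3. Change the bracketed margin to 0.7% in Strengths and limitations, Sample size and justification, and Statistical analyses, keeping 8 mmol/mol as the decision limit.

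The cost is wording only, with no change to margin, sample size or analysis. The real price is a narrower permitted claim: the remission test has only about 25 to 27% power at 48 to 53 per arm (one-sided 0.05), or 16 to 18% at one-sided 0.025, so it will probably be inconclusive even if the arms are equal.

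### The primary non-inferiority rule is not fixed: the margin is written as two unequal values, and alpha 0.05 has no sidedness or confidence level

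*Protocol article*

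**What the plan says.** The section Sample size and justification sets the margin: "The non-inferiority margin (delta) for HbA1c is set at 8 mmol/mol (0.8" per cent, in brackets. It takes its variability from an earlier diet trial, "with a SD of 13.3 mmol/mol (1.2" per cent, again in brackets. It then says: "If we assume the same SD in the present study, we need to randomise 96 study participants to achieve sufficient power", using "a test procedure based on the estimation of a CI based on the t-distribution". The error rates come last: "For the calculation, we used a significance level (alpha) of 0.05 and a target power (1-beta) of 90" per cent. A 10% drop-out allowance brings the plan to 106 participants.

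The section Statistical analyses names the primary analysis, an ANCOVA of 12-month HbA1c adjusted for baseline HbA1c and centre, and repeats the margin in the same double form: "The non-inferiority margin is 8 mmol/mol (0.8" per cent). It gives no alpha, sidedness or confidence level. The same pair of values, 8 mmol/mol and 0.8%, also stands in the strengths and limitations box.

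**The concern.** In a non-inferiority trial, the margin and the confidence limit compared with it are the whole decision rule. Here neither has a single value. An alpha of 0.05 can mean a one-sided 5% test (upper limit of a 90% CI) or a two-sided 5% level (upper limit of a 95% CI, which tests at one-sided 2.5%). The margin can be read as 8 mmol/mol or as 0.8%, which is a larger difference.

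Two analysts following the article faithfully could reach opposite conclusions from the same data. The trial is open-label and has no data monitoring committee, so it is all the more useful to have the rule fixed in print before the 12-month results are analysed.

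**Working it through.** **Inputs.** From Sample size and justification: margin 8 mmol/mol or 0.8%; SD 13.3 mmol/mol or 1.2%; alpha 0.05; power 90%; 96 participants. From Randomisation: 1:1 allocation, so 48 per arm. Assumed, because not stated: true difference 0.

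**1. Are the two margins equal?** The SD pair gives 1.2/13.3 = 0.0902 percentage points per mmol/mol.
- 8 × 1.2/13.3 = 0.72%. Allowing for rounding of the SD pair, the range is 8 × 1.15/13.35 = 0.69% to 8 × 1.25/13.25 = 0.75%.
- 0.8 × 13.3/1.2 = 8.87 mmol/mol.

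So the pair does not match: 0.72% rounds to 0.7%, and only the extreme end of the rounding range (0.755%) would round to 0.8%.

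**2. Reproducing the 96.** Formula per arm: n = 2 × (z for 1 − α + z for power)² × (SD/margin)², with z = 1.2816 for 90% power and z = 1.645 (one-sided 5%) or 1.960 (one-sided 2.5%).

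| Units used | One-sided 5% (90% CI) | One-sided 2.5% (95% CI) |
|---|---|---|
| 8 and 13.3 mmol/mol | 47.3 → 48 per arm, **96** | 58.1 → 59 per arm, 118 |
| 0.8% and 1.2% | 38.5 → 39 per arm, 78 | 47.3 → 48 per arm, **96** |

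The stated figure is reproduced twice, once in each unit, with a different alpha each time. The larger margin relative to SD in percent (0.8/1.2 = 0.667, against 8/13.3 = 0.602) almost exactly offsets the stricter alpha.

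**3. Power at 48 per arm (noncentral t, 94 df, no covariate adjustment).**
- mmol/mol figures: 90.0% at one-sided 5%; 83.1% at one-sided 2.5%.
- Percent figures: 89.8% at one-sided 2.5%.

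**4. Effect of the planned ANCOVA.** If the baseline to 12-month correlation is r, the residual variance is multiplied by 1 − r². With the 8 mmol/mol margin and a 95% CI, 48 per arm reaches 90% when 58.1 × (1 − r²) ≤ 48, so r ≥ 0.42 by the normal formula, or about 0.43 to 0.44 by the noncentral t. The article gives no value for r.

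**5. Effect on the verdict.** SE = 13.3 × √(2/48) = 2.71 mmol/mol. Half-widths: 1.661 × 2.71 = 4.51 (90% CI) and 1.986 × 2.71 = 5.39 (95% CI). Non-inferiority is declared when the observed difference (eHealth minus face-to-face) is below:

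| Margin | 90% CI | 95% CI |
|---|---|---|
| 8 mmol/mol | 8 − 4.51 = 3.5 | 8 − 5.39 = 2.6 |
| 0.8%, taken as 8.87 mmol/mol | 4.4 | 3.5 |

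An observed difference of 3 mmol/mol passes with a 90% CI and fails with a 95% CI on the 8 mmol/mol margin.

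**The case against.** The strongest defence is that nothing in the sample size is miscalculated. The 96 reproduces, a one-sided 5% test may be what was intended, and a confidence level can often be left to the analysis plan. The bracketed percentage may be only a rough conversion: mmol/mol comes first throughout, and the comparison of the margin with drug effects is made in mmol/mol alone.

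Part of this stands. The 96 is not an arithmetic error, and mmol/mol is the natural unit to treat as primary. But the point is more than omitted detail. The article itself states an alpha, a power and a number whose meaning depends on the missing word, and it gives the decision threshold as two values that its own SD pair shows to be unequal.

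Three stronger readings are tempting and are not supported:
- **That 96 works only with a one-sided 5% test, so a 90% CI must be meant.** The percent figures give 96 with a 95% CI. The number does not reveal the rule.
- **That the trial is underpowered.** The 83% belongs to an unadjusted comparison in one of the readings. The planned analysis adjusts for baseline HbA1c and may recover the loss. With r unreported, this cannot be settled either way.
- **That the drop-out allowance is wrong.** 106 × 0.9 = 95.4 falls short of 96 by less than one participant, which is immaterial.

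**Conclusion.** The concern holds as an inconsistently stated decision rule, not as a faulty sample size. The margin is wrong as written in one of its two units (8 mmol/mol is about 0.72%, range 0.69 to 0.75%; 0.8% is about 8.9 mmol/mol). The sidedness of alpha and the confidence level are not stated, and the sample size cannot supply them. On the 8 mmol/mol margin, the choice moves the passing threshold between 3.5 and 2.6 mmol/mol and unadjusted power between 90% and about 83%.

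These figures assume SD 13.3 mmol/mol, 96 evaluable participants and a true difference of 0. Recovering about 90% power with a 95% CI needs a baseline to 12-month correlation of about 0.43 or more, which is an assumption without a source in the article.

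**What to change.** Before any 12-month data are seen:

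1. Make 8 mmol/mol the binding margin and correct the percent equivalent to about 0.7% wherever the pair appears (strengths and limitations, Sample size and justification, Statistical analyses).
2. In Sample size and justification and in Statistical analyses, state the one-sided alpha and the matching two-sided CI level. Say that non-inferiority is concluded if the upper limit for eHealth minus face-to-face lies below 8 mmol/mol. Which level applies is for the sponsor to declare; the article does not settle it.
3. State the power for that rule. If one-sided 5%: 90%, with the 95% CI reported as well. If one-sided 2.5%: about 83% before any gain from ANCOVA, with the assumed correlation given if a gain is claimed.

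The cost is wording only. The downside is that the stated power may look less favourable if the 95% CI is the rule.

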### Statistical analyses

For the primary outcome, the continuous variable HbA1c is analysed for non-inferiority using ANCOVA, with HbA1c at 12 months as the dependent variable and the group as the independent variable. The analysis will be adjusted for baseline HbA1c and study centre to account for stratified randomisation. The non-inferiority margin is 8 mmol/mol (0.8%). If a participant is taking medication to lower blood glucose, that participant’s HbA1c will be adjusted for the average blood glucose-lowering effect of the medication used, according to the meta-analysis by Tsapas and colleagues.^29^ The analysis is performed according to the intention-to-treat principle with imputation of missing values using multivariate imputation by chained equations.^31^ The same analysis will be performed on the full analysis set, that is, all randomised participants with HbA1c measurements at baseline and 12 months, as a sensitivity analysis. The intention-to-treat population is defined as all study participants that were randomised.

The secondary outcome diabetes remission in per cent will be tested for non-inferiority with a non-inferiority margin of 10 percentage points, followed by a test for superiority. The other secondary outcomes will be tested for superiority only.

For the cost-effectiveness analysis, the incremental costs per QALYs gained is the main outcome. Costs include the total diet replacement portions used, meetings with the study team including travel time, time taken by the study team to assess and provide feedback on participants’ measurements each week, other healthcare visits and hospital days, blood glucose-lowering and blood pressure-lowering medications, costs of HbA1c analyses and scales, blood pressure monitors and blood glucose metres. Participants will answer the SF-36 and EQ-5D-5L questionnaires to analyse how they experience their health and quality of life. Costs are analysed based on the intention-to-treat principle. Mean costs are calculated for each group, with cluster-adjusted standard errors for each cost item. Incremental costs per QALY after 2 years are given as the difference in total costs of the groups after 2 years divided by the difference in QALYs. The cost per QALY gained is compared with the Swedish threshold of SEK 500 000. If the ratio is below the threshold, the intervention is categorised as cost-effective. If both interventions are cost-effective, the most effective one is recommended for introduction into normal healthcare.

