### Inclusion criteria

Type 2 diabetes with a duration of 6 years or less (diagnosis based on two documented diagnostic tests of either HbA1c, fasting blood glucose or 2-hour blood glucose after an oral glucose tolerance test (OGTT) using WHO diagnostic criteria).^11^Age 20–70 years.Body mass index (BMI)≥27 kg/m^2^.HbA1c≥43 mmol/mol (6.1%) at baseline if taking glucose lowering medication.HbA1c≥48 mmol/mol (6.5%) at baseline if not on glucose lowering medication.

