#### Medication discontinuation

Glucose-lowering medication is discontinued under the supervision of the study physician when total diet replacement is started. In most patients with short-term diabetes, blood glucose levels improve within a week if they adhere to the total diet replacement.^1^ In addition, diabetes remission can only be diagnosed if the patient is without such medication.^3^ However, if blood glucose levels rise, glucose-lowering medication is reintroduced (online supplemental material 2). All anti-hypertensive medication and diuretics are discontinued when starting the total diet replacement, as many people suffer from hypotension and orthostasis after starting a very low-calorie diet. However, participants do not discontinue blood pressure medications taken for reasons other than hypertension (eg, beta-blockers used to treat heart disease are not discontinued). Based on blood pressure measurements during the study, medication will be restarted if blood pressure rises (online supplemental material 3), following criteria adapted from the DiRECT study.^15^

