### Primary outcome

The primary outcome is HbA1c as a continuous outcome at 12 months.

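### The primary ANCOVA mixes on-drug and off-drug baseline HbA1c, and the plan does not say whether the drug-effect correction reaches baseline; if it does not, a little precision is lost

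*Protocol article*

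**What the plan says.** All references are to the protocol article.

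- **Primary outcome:** "The primary outcome is HbA1c as a continuous outcome at 12 months".
- **Statistical analyses, covariates:** "The analysis will be adjusted for baseline HbA1c and study centre to account for stratified randomisation". No term for medication at entry is named.
- **Statistical analyses, drug correction:** "If a participant is taking medication to lower blood glucose, that participant’s HbA1c will be adjusted for the average blood glucose-lowering effect" of the drug used, with the effect taken from a cited meta-analysis. The sentence does not say whether it covers the 12-month value, the baseline value or both.
- **Inclusion criteria:** two entry thresholds, "HbA1c≥43 mmol/mol (6.1%) at baseline if taking glucose lowering medication" and "HbA1c≥48 mmol/mol (6.5%) at baseline if not on glucose lowering medication".
- **Medication discontinuation:** "Glucose-lowering medication is discontinued under the supervision of the study physician when total diet replacement is started". Drugs are reintroduced if blood glucose rises.
- **Sample size and justification:** commonly used drugs are said to lower HbA1c by at least 8 mmol/mol. The trial is sized on an SD of 13.3 mmol/mol with no allowance for covariates.

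**The concern.** A measured baseline of 50 mmol/mol means different things in a treated and an untreated person. With the article's own minimum drug effect of 8, the treated person would be at about 50 + 8 = 58 off drug. The entry thresholds show the same mismatch: a treated person at the cut-off of 43 corresponds to about 43 + 8 = 51 off drug, above the untreated cut-off of 48, although the measured value is 5 lower.

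The correction puts 12-month HbA1c on a drug-free scale. If baseline is left as measured, the model predicts the same outcome for both people. The covariate then loses part of its correlation with the outcome, and the interval set against the 8 mmol/mol margin is wider than it has to be. What is at stake is precision, plus an unambiguous definition of the main covariate in the primary analysis.

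**Working it through.** **1. Reproduce the planned size.** Inputs from Sample size and justification: margin 8, SD 13.3, alpha 0.05, power 90%, 1:1 allocation. Taking alpha as one-sided, with a true difference of zero:

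n per arm = 2 × 13.3² × (1.645 + 1.282)² / 8² = 47.3, rounded up to 48, so 96 in total.

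This matches. (One-sided 0.025 gives 59 per arm, 118 in total, which does not.) Adding 10% gives 96 × 1.10 = 105.6, so 106. Power at 48 per arm by the noncentral t is 0.900. No baseline covariate enters these figures.

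**2. Assumed inputs.** The article gives neither the share medicated at entry nor the correlation of baseline with 12-month HbA1c. Assumed: 50% or 70% on drug before the entry cut-offs; drug effect 8 (the article's minimum) or 12; SD of drug-free baseline 12; correlation of drug-free baseline with 12-month HbA1c 0.3 or 0.5; total SD 13.3; no prognostic effect of medication beyond its effect on the baseline reading.

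**3. Large-sample residual variance, as a fraction of total variance.** The cut is computed from unrounded fractions. Power is at 96 with one-sided 0.05.

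| On drug | Effect | Corr. | Measured baseline | + yes/no term | Corrected baseline | Cut | Power |
|---|---|---|---|---|---|---|---|
| 50% | 8 | 0.3 | 0.927 | 0.910 | 0.910 | 1.9% | 0.918 → 0.922 |
| 50% | 8 | 0.5 | 0.798 | 0.750 | 0.750 | 6.0% | 0.948 → 0.959 |
| 50% | 12 | 0.3 | 0.945 | 0.909 | 0.909 | 3.8% | 0.914 → 0.923 |
| 50% | 12 | 0.5 | 0.848 | 0.749 | 0.749 | 11.8% | 0.937 → 0.959 |
| 70% | 8 | 0.3 | 0.927 | 0.911 | 0.911 | 1.7% | 0.918 → 0.922 |
| 70% | 8 | 0.5 | 0.795 | 0.751 | 0.751 | 5.6% | 0.949 → 0.958 |
| 70% | 12 | 0.3 | 0.946 | 0.910 | 0.910 | 3.9% | 0.913 → 0.923 |
| 70% | 12 | 0.5 | 0.851 | 0.749 | 0.749 | 12.0% | 0.937 → 0.959 |

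The yes/no column and the corrected-baseline column agree in every row, so under these assumptions either remedy recovers the whole loss.

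**4. Charge for the extra parameter.** With q covariates and N = 96, chance imbalance inflates the variance of the group difference by about 1 + q/(N − q − 3). Going from q = 2 to q = 3 multiplies it by (1 + 3/90)/(1 + 2/91) = 1.011. The smallest and largest cuts in the table become 1 − 0.983 × 1.011 = 0.6% and 1 − 0.880 × 1.011 = 11%. Direct simulation of trials of 96 with the yes/no term gave about 0.5–10%.

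**5. In HbA1c units.** With the planning SD, SE = 13.3 × √(2/48) = 2.71. The one-sided 95% bound lies 1.661 × 2.71 = 4.51 from the estimate. A 10% variance cut gives 4.51 × √0.90 = 4.28, which is 0.23 mmol/mol closer; a 0.5% cut gives about 0.01. On the planning SD, a 10% cut moves power from 0.900 to 0.925, or the N for 90% power from 96 to 86. A 1% cut moves them to 0.902 and 94.

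**6. If medication is itself prognostic.** Suppose drug use at entry predicts a 4 mmol/mol higher 12-month HbA1c. In the first row the fractions become 0.954 (measured), 0.902 (corrected) and 0.879 (yes/no term). Correction alone then leaves part of the gain behind. The net cut from the yes/no term at 96 is about 5–19%.

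**The case against.** The strongest reply is that the correction sentence names no time point. It stands close after the sentence that brings baseline HbA1c into the model, so it can be read as covering both values. On that reading the table shows nothing left to recover, unless medication is prognostic in its own right. This stands: a reader might infer that the plan definitely leaves baseline uncorrected, and the text does not support that. It leaves the matter open.

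A second reply is that such detail belongs in an analysis plan that is not shown. That is fair for the reach of the correction. It is weaker for the covariates, which the article itself fixes as baseline HbA1c and study centre.

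Third, adjusting for the baseline outcome and the stratification factor is a sound, conventional model. That also stands. A reader might infer bias or an underpowered trial, and neither follows: allocation is random, and 96 rests on the unadjusted SD.

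Fourth, one might prefer a finer grading of medication (none, one, two or more drugs). At 96 participants that can cost as much as it gains. Simulated variance ratios, with the grading against without it, were 1.008 and 0.981 for a drug effect of 8 (correlation 0.3 and 0.5), and 0.987 and 0.922 for an effect of 14. A single yes/no term is the safer choice.

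**Conclusion.** The point holds as a small matter of efficiency and clarity. The primary covariate is not uniquely defined: it is either HbA1c as measured, mixing treated and untreated readings, or HbA1c corrected for drug effect. If it is as measured while the outcome is corrected, precision is lost.

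The size depends on inputs the article does not give. Within the ranges assumed above, the net variance cut at 96 is about 0.5–10%. It is more if medication is itself prognostic (about 5–19% for a 4 mmol/mol effect), and about zero if medication adds nothing to baseline HbA1c or baseline is already corrected. A correlation of 0.6, outside the main range, raised the large-sample cut to as much as 19% without a prognostic effect. The validity of the comparison and the figures of 96 and 106 are unaffected.

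**What to change.** State, before the primary analysis, whether the drug-effect correction applies to baseline HbA1c. Then do one of the following:

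- apply to baseline HbA1c the same correction as to 12-month HbA1c; or
- add one yes/no term for glucose-lowering medication at baseline to the primary ANCOVA and to the imputation model.

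Either is enough if medication has no prognostic effect of its own. The yes/no term also captures such an effect and estimates the shift from the trial's data. If the correction was always meant to cover baseline, a short clarifying phrase settles the definition.

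The yes/no term costs one degree of freedom, about 1% of variance at 96. It needs no new data, because medication status must already be known to apply the inclusion criteria. Correcting baseline costs no degree of freedom, but it requires the drugs taken at entry to be on record.
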